### Outcomes

The primary endpoint is the mean total depression score using the 17-item version of the Hamilton Depression Rating Scale (HAM-D) [22], after six weeks. Severity of symptoms will be assessed by a blinded investigator (psychologist) from the Clinic for Psychiatry and Psychotherapy, Charité University Medical Center. The secondary end points are the mean HAM-D total scores after two and four weeks, response (decrease of 50% or more from baseline HAM-D score) and remission (HAM-D scores ≤ 7) rates, Beck Depression inventory (BDI) [23] total score and mean SF-12 Health Survey (SF-12) at weeks two, four and six.

Adverse events will be collected during the study and will form part of the secondary endpoint data in determining the safety of homeopathic medicines. Serious adverse effects from homeopathic medicine were not observed on the non-inferiority trial [17] and are not expected during the current study. Participants' treatment expectations at baseline will also be assessed.

### Randomization and blinding

A non-stratified block randomization with variable block lengths will be carried out, with a 2:1:1:2 ratio (aiming at exposing a smaller number of participants to placebo treatment) for group 1: group 2: group 3: group 4 (i.e. 76:38:38:76 patients). The randomization list was generated with SAS/BASE Software (SAS Inc., Cary NC, USA), by a statistician not further involved in the study. The patients will be assigned in sequential order to the treatment groups.

The patients, the psychiatrist and the statistician will remain blinded from the identity of the four treatment groups until the end of the study. The study clinical investigator will be unmasked for the case history type I or II. The randomization list will be kept strictly confidential. Only the study pharmacist and the statistician who generated the randomization list have access to the randomization list. During the study, unblinding will only occur in the case of a patient emergency using sealed emergency envelopes.

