### Statistical Analysis

The following primary comparisons will be conducted between the following groups: The specific effect of homeopathic medicines compared to placebo (double blind comparison), where essentially the groups 1+3 will be compared to the groups 2+4. The effect of the homeopathic case history (single-blind comparison), where essentially groups 1+2 (case history type I) are compared to the groups 3+4 (case history type II).

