#### Sample size calculation

For this study we assumed that the verum treatment is better than placebo by 2.7 ± 6.0 (mean ± standard deviation) HAM-D score points after 6 weeks (corresponding to a SMD = 0.45), that type II case history is better than type I by 2.7 ± 6.0 score points (SMD = 0.45), and that both effects do not interact. If so, a Bonferoni-adjusted F-Test (multiple significance level α = 0.05, two-sided) has a power of 83.5% to detect the difference between verum and placebo and a power of 85.0% to detect the difference in case history taking, if 68 patients are included in groups 1 and 3, and 34 patients are included in groups 2 and 4. This leads to a total number of 228 patients, if one allows for a 10%drop-out rate per group.

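### The allocation of 76:38:38:76 to groups 1 to 4 contradicts the 2:1:2:1 split in the sample-size section and, with the group labels in the analysis section, its own aim of fewer placebo patients

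*Protocol article*

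**What the plan says.** Three places in the protocol article fix the size or the content of the four groups.

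- **Randomization and blinding** gives the ratio "with a 2:1:1:2 ratio (aiming at exposing a smaller number of participants to placebo treatment" and spells out the counts: "for group 1: group 2: group 3: group 4 (i.e. 76:38:38:76 patients". The same section says that the randomisation list has already been generated, and that "The study clinical investigator will be unmasked for the case history type I or II".
- **Statistical Analysis** defines the medicine comparison as one "where essentially the groups 1+3 will be compared to the groups 2+4". For case history, "groups 1+2 (case history type I) are compared to the groups 3+4 (case history type II".
- **Sample size calculation** derives power "if 68 patients are included in groups 1 and 3, and 34 patients are included in groups 2 and 4" and allows 10% drop-out per group, for a total of 228. It assumes that "verum treatment is better than placebo by 2.7 ± 6.0 (mean ± standard deviation) HAM-D score points after 6 weeks" and that "type II case history is better than type I by 2.7 ± 6.0 score points", with no interaction.

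The analysis of the primary endpoint is a model containing medicine, case history and their interaction, with Bonferroni-Holm adjustment over the two hypotheses. Figure 1, which illustrates the groups, was not readable in the text examined.

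**The concern.** The randomisation section makes group 3 small and group 4 large; the sample-size section does the reverse. The analysis section agrees with the sample-size section: if groups 1 and 3 are verum, enlarging those two groups is how one reduces placebo exposure. The randomisation section enlarges groups 1 and 4 instead, while giving reduced placebo exposure as its reason.

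What is at stake is which patients receive placebo, whether the two factors of the 2 × 2 design are balanced against each other, and what the stated medicine comparison estimates. Because the list already exists, one of the two versions may be in use.

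**Working it through.** **1. Reproduce the plan's total.** Inputs from Sample size calculation: 68 or 34 evaluable patients per group, 10% drop-out.

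- 68 / 0.9 = 75.6, rounded up to 76
- 34 / 0.9 = 37.8, rounded up to 38
- 76 + 38 + 76 + 38 = 228, as stated

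The total is therefore built on 76:38:76:38. The randomisation section also sums to 228, but with groups 3 and 4 exchanged. This conflict needs no group labels.

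**2. Try each labelling.** Case-history types are as in Statistical Analysis (1+2 type I, 3+4 type II).

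| Verum groups | Split | Verum | Placebo | Verum share, type I / type II |
|---|---|---|---|---|
| 1 and 3 | 76:38:38:76 | 76 + 38 = 114 | 38 + 76 = 114 | 76/114 = 2/3; 38/114 = 1/3 |
| 1 and 3 | 76:38:76:38 | 76 + 76 = 152 | 38 + 38 = 76 | 2/3; 2/3 |
| 1 and 4 | 76:38:38:76 | 76 + 76 = 152 | 38 + 38 = 76 | 2/3; 2/3 |
| 1 and 4 | 76:38:76:38 | 76 + 38 = 114 | 38 + 76 = 114 | 2/3; 1/3 |

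The second row satisfies the analysis and sample-size sections but not the randomisation section. The third satisfies the randomisation section but neither of the others. In that case group 1 is verum/type I, group 2 placebo/type I, group 3 placebo/type II and group 4 verum/type II, so 1+3 against 2+4 is (verum I − placebo I) − (verum II − placebo II), the interaction contrast. No row satisfies all three sections.

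**3. Consequences of the first row** (stated allocation, printed labels).

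- Placebo excess: 114 − 76 = 38 patients.
- Correlation of verum with type II: (38 × 38 − 76 × 76) / 114² = −4332 / 12996 = −1/3. Under 2:1:2:1 it is 0.
- Odds of verum: 76:38 = 2:1 under type I and 1:2 under type II.
- Crude pooled comparison: type II makes up 38/114 = 1/3 of verum and 76/114 = 2/3 of placebo. With the plan's 2.7-point case-history effect, the medicine difference shifts by 2.7 × (2/3 − 1/3) = 0.9 points, so 2.7 would appear as 1.8.

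**4. Planned model.** With both factors and their interaction, each main effect is an equally weighted contrast of four cell means, with variance (σ²/4) × Σ(1/n). With σ = 6.0 and the evaluable counts:

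SE = √[9 × (2/68 + 2/34)] = √0.794 = 0.891 points.

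The sum depends only on there being two cells of 68 and two of 34, not on which group holds which. The SE is 0.891 for both factors under both splits.

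**5. Can the stated powers identify the intended split?** The plan states 83.5% (medicine) and 85.0% (case history). Simulated Holm power (20,000 runs) with the interaction in the model is 83.7% and 83.5% under 2:1:2:1, and 82.7% and 83.2% under 2:1:1:2, both with the printed labels. All four lie within 2 points of the stated values, so the powers do not decide the matter.

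**The case against.** The strongest defence is that Figure 1 may define groups 1 and 4 as verum. The randomisation section would then be right, and there would be no placebo excess, no correlation between factors and no guessing problem. This stands as far as it goes: those three consequences are conditional on the printed labels. It does not remove the contradiction, because the randomisation and sample-size sections conflict on counts alone, and this reading moves the error into the medicine contrast and the sample-size group numbers.

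Three stronger readings are tempting, and the document does not support them.

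- *The primary estimate is biased.* A reader might infer this from the 0.9-point shift. That shift belongs to a comparison of pooled groups that ignores case history. The analysis section names the pooled groups only as the essence of the comparison; the specified model contains both factors and separates them.
- *Power for case history is lost.* In an additive model at a plain two-sided 0.025 level, it does fall from 83.0% to 77.9%. The plan specifies the interaction and Holm. With the interaction in the model, the SE is the same under both splits.
- *The double-blind comparison is unmasked.* Guessing from case-history type would be right 67% of the time, but always guessing verum under 2:1:2:1 is also right in 152/228 = 67%. What remains is that the best guess would differ by case-history type. That requires knowledge of the ratio and the labels, and gives odds, not certainty. It concerns the clinical investigator; the HAM-D is rated by a blinded psychologist and the list is confidential.

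**Conclusion.** The contradiction is real and is not something that an article leaves to a fuller document: the stated figures are incompatible. Either the allocation is wrong, or both the medicine contrast and the sample-size group numbers are wrong.

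On the printed labels, and if the stated counts are implemented, 38 more patients than intended receive placebo, the factors correlate at −1/3, and case-history type carries some information about the medicine for the treating investigator. If groups 1 and 4 are verum, none of that follows, but the medicine comparison as written describes the interaction. In neither case is the planned model-based estimate of a main effect biased or less precise, provided that the factors are coded from the true group contents. The document alone does not show which section is in error.

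**What to change.** Before choosing a side, have the independent statistician who generated the list check it against Figure 1. Then:

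- if groups 1 and 3 are verum, correct Randomization and blinding to 2:1:2:1 (76:38:76:38), and regenerate the list if it follows 2:1:1:2 and has not been used;
- if groups 1 and 4 are verum, keep 2:1:1:2 and correct the contrast in Statistical Analysis to 1+4 against 2+3 and the group numbers in Sample size calculation to 68 in groups 1 and 4, 34 in groups 2 and 3;
- if a 2:1:1:2 list with groups 1 and 3 as verum is already in use, keep both factors in every model, make no unadjusted pooled comparison, and restate group sizes and power for that split.

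The cost is one check of the list and a short text correction, or a new list if the existing one is wrong and unused. No extra patients are needed: the total stays at 228.

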### Data management

Data management services will be performed by the study center at the Institute for Social Medicine, Epidemiology and Health Economics - Charité University in accordance with the ICH-Guidelines for Good Clinical Practice and DIN EN ISO 2001.

### Statistical Analysis

The following primary comparisons will be conducted between the following groups: The specific effect of homeopathic medicines compared to placebo (double blind comparison), where essentially the groups 1+3 will be compared to the groups 2+4. The effect of the homeopathic case history (single-blind comparison), where essentially groups 1+2 (case history type I) are compared to the groups 3+4 (case history type II).

#### Analysis for the primary endpoint

Statistical analysis will be by intention-to-treat, including all patients randomized, regardless whether or not they adhered to the treatment protocol or provided complete data sets. Only patients who withdraw their consent to use their personal data can be excluded from the analysis.

To indicate, whether or not the randomisation process leads to prognostically balanced treatment groups, all baseline parameters will be compared by two sided Chi-square-tests (if nominally scaled) or Kruskal-Wallis-tests (if ordinally or continuously scaled). The respective p-values are descriptive in nature, not confirmative.

The primary endpoint will be analysed by a two-factorial analysis of covariance (ANCOVA), modeling time (3 levels: weeks 2, 4 and 6) as a within-group-factor, type of case history (2 levels: types I and II), type of medicine (2 levels: verum and placebo), and their respective interaction as between-group factors, and baseline value and patient's expectation as linear covariates. Within this model generalized estimation equations (GEE) [24] will be used to estimate the 6-week differences between verum and placebo, and between both types of case history. Two-sided p-values and confidence intervals for both hypotheses will be adjusted by the Bonferoni-Holm procedure [25]. As no interim analyses are planned there is no need for further multiple adjustments. The multiple level of significance is set at α = 0.05 (two-sided).

#### Sample size calculation

For this study we assumed that the verum treatment is better than placebo by 2.7 ± 6.0 (mean ± standard deviation) HAM-D score points after 6 weeks (corresponding to a SMD = 0.45), that type II case history is better than type I by 2.7 ± 6.0 score points (SMD = 0.45), and that both effects do not interact. If so, a Bonferoni-adjusted F-Test (multiple significance level α = 0.05, two-sided) has a power of 83.5% to detect the difference between verum and placebo and a power of 85.0% to detect the difference in case history taking, if 68 patients are included in groups 1 and 3, and 34 patients are included in groups 2 and 4. This leads to a total number of 228 patients, if one allows for a 10%drop-out rate per group.

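### The stated power (83.5% and 85.0%) does not belong to the Bonferroni test it is attributed to; verum-placebo is about right only under Holm with both effects real

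*Protocol article*

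**What the plan says.** The Sample size calculation assumes that "the verum treatment is better than placebo by 2.7 ± 6.0 (mean ± standard deviation) HAM-D score points after 6 weeks", that "type II case history is better than type I by 2.7 ± 6.0 score points (SMD = 0.45"), and that "both effects do not interact". On those assumptions it names the test as "a Bonferoni-adjusted F-Test (multiple significance level α = 0.05, two-sided") and says that it "has a power of 83.5% to detect the difference between verum and placebo and a power of 85.0" per cent for case history. The cells behind these figures are 68 patients in groups 1 and 3 and 34 in groups 2 and 4.

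The section on the analysis of the primary endpoint describes a different multiplicity procedure: "Two-sided p-values and confidence intervals for both hypotheses will be adjusted by the Bonferoni-Holm procedure". Its model has both factors "and their respective interaction as between-group factors".

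**The concern.** The two sections name different procedures. Single-step Bonferroni tests each hypothesis at 0.025. Holm also allows 0.05 for one hypothesis once the other has been rejected at 0.025. For a reader who checks the power against the test named beside it, the verum-placebo figure is more than five points too high.

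If Holm was meant, part of the medicine's power comes from the case-history hypothesis being rejected as well. The Background says that neither component's specific effect has been investigated in depression, so it matters how the power changes if one effect is absent. Verum versus placebo is one of the two confirmatory comparisons, and a null result there would be judged partly against the stated power.

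**Working it through.** **Inputs.** Effect 2.7, SD 6.0 and SMD 0.45 for each factor, with no interaction; evaluable cells 68/34/68/34 for groups 1 to 4, total 204 (Sample size calculation). Verum versus placebo is groups 1+3 against 2+4, so 136 vs 68. Case history is groups 1+2 against 3+4, so 102 vs 102 (Statistical Analysis). Overall level 0.05 two-sided; two hypotheses, so 0.025 each under Bonferroni.

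**Total sample size.** 68/0.9 = 75.6, rounded up to 76; 34/0.9 = 37.8, rounded up to 38; 2 × (76 + 38) = 228. This reproduces.

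**Step 1: the named test, without interaction.** Noncentrality δ = 0.45 × √(n₁n₂/(n₁+n₂)). Power is from the noncentral t with 200 df, equivalent to the 1-df F-test.

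- Medicine: δ = 0.45 × √(136 × 68/204) = 3.030. Power is 77.9% at 0.025 and 85.4% at 0.05.
- Case history: δ = 0.45 × √(102 × 102/204) = 3.214. Power is about 83% at 0.025 (83.5% by normal approximation) and 89.2% at 0.05.

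**Step 2: the named test, with the planned interaction.** With equal cell weights, the standard error of either main effect is σ × 0.5 × √(2/68 + 2/34) = 0.1485σ. So δ = 0.45/0.1485 = 3.030 for both factors, and power is 77.9% for both. The standard errors are equal, so this model cannot give two different powers for the same effect size.

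**Step 3: Bonferroni-Holm, both effects 2.7.** For independent tests, power of A = P_A(0.025) + [P_A(0.05) − P_A(0.025)] × P_B(0.025).

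- With interaction: 0.779 + (0.854 − 0.779) × 0.779 ≈ 0.837 for both factors; simulation gives 83.7% for both.
- Additive, medicine: 0.779 + 0.075 × 0.830 ≈ 0.841; simulation gives 84.1%.
- Additive, case history: 0.830 + (0.892 − 0.830) × 0.779 ≈ 0.878; simulation gives 87.9%.

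The Randomization section's 2:1:1:2 ratio makes groups 1 and 4 the large ones, so the evaluable cells become 68/34/34/68. Then δ is 3.030 for both factors in either model, and the two estimates are correlated (1/3). The product formula no longer applies; simulation gives 83.1% for both with interaction and 83.0% for both without.

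**Step 4: Holm, case-history effect zero.** Medicine: 0.779 + 0.075 × 0.025 ≈ 0.781, about 78%. Simulation agrees for both sets of cells.

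| Setting | Verum-placebo | Case history |
|---|---|---|
| Stated | 83.5% | 85.0% |
| Bonferroni, 68/34/68/34, additive | 77.9% | about 83% |
| Bonferroni, 68/34/68/34, interaction | 77.9% | 77.9% |
| Holm, 68/34/68/34, additive | 84.1% | 87.9% |
| Holm, 68/34/68/34, interaction | 83.7% | 83.7% |
| Holm, 68/34/34/68, interaction | 83.1% | 83.1% |
| Holm, case history null | about 78% | not applicable |

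No row gives the stated pair.

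**The case against.** A reader might infer from step 1 that the trial's verum-placebo power is simply 78% and that the stated power is not delivered. The documents do not support that.

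- **Holm is the planned procedure.** The wording in the sample size section, which directly follows the analysis section, may be shorthand for it. Under Holm in the planned model, verum-placebo is 83.1 to 83.7%, within 0.4 points of 83.5%. This stands.
- **The condition that Holm needs is in the text.** The power statement is made conditional on both effects being 2.7 points. It would be wrong to say that this assumption is hidden. What the article does not say is how far the medicine's power depends on it.
- **The case-history gap can be small.** Under single-step Bonferroni without interaction it is about 2 points, and Holm in the additive model exceeds 85.0%. The wider gap of 7.1 points combines the planned interaction with a multiplicity procedure that the analysis section does not use. This also stands. Even so, in the planned model under Holm, case history is 83.1 to 83.7%, not 85.0%.
- **Covariates could raise power.** The model adjusts for baseline and expectation. If 6.0 is an unadjusted SD, a residual SD of about 5.6 would give 83.5% at 0.025. The article does not say which SD it means and claims no such gain, so this neither rescues the figure nor fixes 77.9% as the power of the planned analysis.

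**Conclusion.** The concern holds as a mismatch between the stated power and the test it is attributed to. With SMD 0.45 and the stated cells, single-step Bonferroni gives verum-placebo 77.9%, which is 5.6 points below the stated figure (type II error 22.1% instead of 16.5%). The figure is approximately right only under Holm with both effects at 2.7 points. The 85.0% for case history is not reproduced in the planned model with interaction; it is 1.3 to 1.9 points too high there. If case history has no effect, verum-placebo power under Holm is about 78%.

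These results take SD 6.0 as the SD that applies to the week-6 comparison, equal cell weights when the interaction is fitted, and 204 evaluable patients. The point concerns how power is reported. It does not show that the trial is too small or that the planned analysis is invalid.

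**What to change.** In the Sample size calculation, name Bonferroni-Holm to match the analysis section. Restate the power as about 83 to 84% for each factor in the planned model if both effects are 2.7 points. Add that verum-placebo power is about 78% if case history has no effect, or under plain Bonferroni. Say whether 6.0 is an unadjusted or a residual SD.

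Reconcile which groups are large (1 and 3 in the sample size section, 1 and 4 in the Randomization section) before the figures are final. The choice moves Holm power in the planned model only between 83.7% and 83.1%.

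The cost is a few sentences and a slightly less favourable power statement. Patient numbers, significance level, endpoint and analysis stay as they are.

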### Regulatory and Ethical approval

#### Regulatory approval

Bundesinstitut für Arzneimittel und Medizinprodukte (BfArM), EudraCT Nr: 2009-017458-11, Submission-Nr.: 4036175.

#### Ethical approval

Ethics Committee, Berlin, Landesamt für Gesundheit und Soziales (LaGeSo): ZS EK 15 099/10. This study is in compliance in with the Helsinki Declaration and with the International Conference on Harmonisation (ICH) - Good Clinical Practice.

## Discussion

For the first time this study evaluates both the specific effect of homeopathic medicines and of a homeopathic case taking in patients with depression. The protocol is in accordance with the EMEA (European Medicines Agency) Guidelines, which recommends placebo-controlled studies and the duration of six weeks for trials investigating medicines for depression [26], considering that during antidepressant pharmacotherapy, one must reckon with a delay of several weeks until sufficient antidepressant effects can be seen [27].

It is the first trial on classical homeopathy after the 15^th ^amendment to the German Medicines Act (Arzneimittelgesetz, AMG) [28]. The study includes all relevant aspects of the CONSORT guidelines for reporting randomized homeopathic trials with parallel groups [29,30]. For ethical reasons, individuals with a previous suicide attempt or a C-SSRS score of 4 or 5 will be excluded and the occurrence of suicide ideation (with the same C-SSRS severity) will determine the premature termination of the patient's participation in the study. Depression severity will be limited to a maximum HAM-D score of 24, because for more severe depression a treatment with antidepressant is recommended [9].

The need of individual prescriptions in classical homeopathy has been considered as 'a severe obstacle for any double-blind trial' [31]. In fact, the selection of a suitable, individualized homeopathic medicine will not be always accomplished during the six weeks of acute treatment, especially under double-blind conditions. However, from an ethical point of view a longer placebo treatment period is problematic.

This study is an experimental study with a focus on efficacy and not a pragmatic trial with a focus on effectiveness. It is an attempt to deal with the challenges of homeopathic research [32] and the results might be useful information in the current discussion about the evidence on homeopathy.

